**Methods/Design:**

The study will be a parallel 3-arm, multi-centre randomized fast-track trial. A total of 120 women with breast cancer related lymphedema will be recruited from 3 centres in Canada and randomized to group 1: Day-time compression garment alone or Group 2: Day-time compression garment + night-time compression bandaging or Group 3: Day-time compression garment + use of a night-time compression system garment. The duration of the primary intervention period will be 12 weeks. The follow-up period after the intervention (weeks 13 to 24) will follow a longitudinal observational design. The primary outcome variables: differences from baseline to week 12 in arm volume and quality of life (Lymphoedema Functioning, Disability and Health Questionnaire: Lymph-ICF). Secondary outcomes include bioimpedance analysis, sleep disturbance and self-efficacy. All measurements are standardized and will be performed prior to randomization, and at weeks 6, 12, 18 and 24.

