### Hypotheses of randomized controlled trial (Phase I)

Standard care plus the addition of CB will provide statistically significant improved management of **arm lymphedema volume** compared to standard care alone at 12-weeks.Standard care plus the addition of NCSG will provide statistically significant improved management of **arm lymphedema volume** compared to standard care alone at 12-weeks.Standard care plus the addition of NCSG will provide statistically significant benefit in **quality of life**, **sleep and self**-**efficacy** over standard care plus CB and standard care alone at 12-weeks.

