## Methods/Design

The study will be a parallel 3-arm, multi-centre randomized fast-track trial including the Cross Cancer Institute (CCI) in Edmonton, Tom Baker Cancer Centre (TBCC) in Calgary and Mount St. Joseph’s Hospital (MSJ) in Vancouver. Women enrolled in the study will be stratified by accruing centre (CCI, TBCC, MSJ) and by lymphedema severity (i.e., mild versus moderate lymphedema as per the classification criteria of International Society of Lymphology) [9, 14], and then randomly assigned to one of three groups: (1) standard care (day-time use of a compression sleeve alone); (2) standard care plus night-time compression by self-administered or assisted CB; (3) standard care plus night-time compression by a traditional NCSG. The duration of the primary intervention period will be 12 weeks. Results from the pilot study and previous case studies suggest a small initial reduction in arm lymphedema volume from administration of the traditional strapped NCSG over the first 6 weeks with stabilization of arm volume (plateau) occurring thereafter. Thus, the 12-week intervention period is deemed sufficient to observe an intervention effect and was chosen to align with current clinical follow-up time periods. Following the 12-week intervention period, participants in the CB and standard care groups will be measured for a NCSG. Participants in these two groups will follow the protocol as per the NCSG group during weeks 13 to 24 [Fig. 3].

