### Secondary endpoints

Secondary endpoints will include bioimpedance analysis, adherence, sleep disturbance, and self-efficacy.

*Bioimpedance analysis* (BIA) will be used to assess *extracellular fluid status* within the arm. BIA measures the impedance of flow from a low alternating electrical current that is applied to the body through a skin electrode. BIA records impedance values for each limb and provides an index that correlates with quantitative measurements of volume increase in limb size seen in the arm with lymphedema [20]. BIA is a simple, painless procedure that takes less than 5 min to perform. BIA has been shown to be a more sensitive measure than arm volume in detecting changes in lymphedema in those with **early mild lymphedema** but less reliable in those with long-standing lymphedema [20]. This measurement will provide information on extracellular fluid changes that complements the data on arm lymphedema volume.

*Sleep disturbance* will be assessed using the RAND Medical Outcomes Survey Sleep Survey [21]. The survey measures 6 key dimensions of sleep: sleep initiation, maintenance, quantity, adequacy, drowsiness, and respiratory impairments (e.g. shortness of breath, snoring). The sleep scale will be used to assess the impact, if any, of wearing night-time compression on sleep quality. The questionnaire takes 5 min to complete.

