### Statistical analyses

Baseline medical and demographic characteristics, arm dominance relative to the lymphadematous arm, and adverse events of the three groups will be compared using one-way ANOVA for continuous data and Pearson’s Chi-square tests for categorical data. The primary analysis will compare the groups with regard to percent excess lymphedema volume and quality of life at 12-weeks using a one-way ANOVA. General linear models will be used to adjust for centre and lymphedema category (mild or moderate), and to evaluate the treatment effect in subgroups defined by the strata. Sleep quality, self-efficacy, and adherence-related outcomes will be analyzed by repeated measures modeling and one-way ANOVA on change scores.

Descriptive data on accrual rates will include the number of women screened for eligibility, the number eligible, the number agreeing to participate, and reasons for refusal to participate. Data on adherence will be collected from all women throughout the 24-week study period. Adherence data will include days worn per week and hours worn per 24-h period, as appropriate, for each of the following: 1) NCSG; 2) CB; 3) day-time compression sleeve. We will also examine adherence during weeks 13 to 24 to the newly assigned NCSG for the standard care and standard care + CB groups, and ongoing adherence during weeks 13 to 24 in the originally assigned standard care + NCSG group. Analyses of primary outcomes will be performed at the end of the RCT portion of the trial. Within group analyses will also be conducted for primary and secondary outcomes from weeks 13 to 24 following completion of all follow-up measures.

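### Sleep and self-efficacy are given two analyses with none named as decisive, and the change-score ANOVA is less precise than adjusting for the baseline already collected

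*Protocol article*

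**What the plan says.** The protocol article, under Statistical analyses, states: "Sleep quality, self-efficacy, and adherence-related outcomes will be analyzed by repeated measures modeling and one-way ANOVA on change scores". The two methods are joined by a plain conjunction. Neither is called main, supportive or sensitivity.

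The outcomes concerned carry a significance hypothesis. The third hypothesis of the randomized phase begins "Standard care plus the addition of NCSG will provide statistically significant benefit in" quality of life, sleep and self-efficacy, and the comparison is "over standard care plus CB and standard care alone at 12-weeks". The Secondary endpoints section fixes their rank: "Secondary endpoints will include bioimpedance analysis, adherence, sleep disturbance, and self-efficacy".

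A baseline value exists for every woman. The Abstract (Methods/Design) says: "All measurements are standardized and will be performed prior to randomization, and at weeks 6, 12, 18 and 24". Only weeks 6 and 12 are randomized comparisons, because after week 12 the bandaging (CB) and standard care groups move to the garment: "Participants in these two groups will follow the protocol as per the NCSG group during weeks 13 to 24" (Methods/Design).

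The only covariates named anywhere are in the sentence just before the one at issue: "General linear models will be used to adjust for centre and lymphedema category (mild or moderate"). The baseline score of the outcome is not named as a covariate for any endpoint.

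**The concern.** There are two separate issues.

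**Precision.** A change score subtracts the whole baseline value whatever its correlation with follow-up. Adjusting for baseline in a regression subtracts only the part that predicts follow-up. Under randomization both estimate the same treatment difference, but the change score is never the more precise of the two when baseline and follow-up variances are equal. A one-way ANOVA by definition has no covariates, so it also leaves out centre and lymphedema severity, by which randomization is stratified.

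**Two tests of one hypothesis.** If both analyses are run and they disagree, nothing in the article says which one answers hypothesis 3. A claim of benefit could rest on whichever was significant, and the error rate per outcome would then exceed the nominal 5%.

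**Working it through.** **The plan's own figures.** The article gives no power for sleep or self-efficacy. Its figures for the two primary outcomes reproduce, which confirms 36 per group and α = 0.05 as inputs.

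- Arm volume (difference 20, SD 25, 36 per group, one-way ANOVA). With means 0, 10 and 20, the noncentrality is 36 × (10² + 0² + 10²)/25² = 11.52. Power on 2 and 105 degrees of freedom is 85.9%; 86% is stated.
- Lymph-ICF (difference 15, SD 22, two-sided Mann-Whitney under normality). The effective n is 36 × 3/π = 34.4 per group and power is 79.6%; 80% is stated.
- Recruitment: 108/(1 − 0.10) = 120, as stated.

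**Step 1: precision.** Assumptions: equal SD at baseline and week 12 (set to 1) and correlation r between them. The article gives no r, so a range is shown.

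- Change score, variance per woman: 2(1 − r)
- Baseline-adjusted, variance per woman: 1 − r²
- Ratio: 2(1 − r)/(1 − r²) = 2/(1 + r)

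Power is for one pairwise comparison with 36 per arm, two-sided α = 0.05, noncentral t, with noncentrality 0.6/√(2 × variance/36). The 0.6 SD difference is an assumption; the article gives no effect size or SD for these scales.

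| r (assumed) | Variance, change score | Variance, baseline-adjusted | Ratio | Power, change score | Power, baseline-adjusted |
|---|---|---|---|---|---|
| 0.3 | 1.40 | 0.91 | 1.54 | 56% | 75% |
| 0.5 | 1.00 | 0.75 | 1.33 | 71% | 83% |
| 0.7 | 0.60 | 0.51 | 1.18 | 90% | 94% |
| 0.8 | 0.40 | 0.36 | 1.11 | 98% | 99% |

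For example, at r = 0.5 the change-score noncentrality is 0.6/√(2 × 1.00/36) = 2.55, against 0.6/√(2 × 0.75/36) = 2.94 with adjustment. A ratio of 1.33 means that the change-score analysis would need one-third more women for the same precision. Any further gain from adjusting for centre and severity is not counted here.

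**Step 2: two analyses.** Null trials were simulated (40,000 per setting, three arms of 36, equal correlation r among baseline, week 6 and week 12). The table shows how often at least one of two tests gave p < 0.05: the week-12 change-score ANOVA, or one form of repeated measures test.

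| r (assumed) | Baseline-adjusted mean of weeks 6 and 12 | Baseline-adjusted week 12 | Mean of weeks 6 and 12 minus baseline |
|---|---|---|---|
| 0.3 | 8.8% | 7.9% | 7.4% |
| 0.5 | 8.3% | 7.3% | 7.4% |
| 0.7 | 8.2% | 6.9% | 7.4% |
| 0.8 | 7.8% | 6.5% | 7.4% |

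A separate run of 20,000 trials gave 9.1% for the first form at r = 0.3, so the range is roughly 6.5–9%. The change-score ANOVA alone stayed at 4.9–5.0%. Two independent tests would give 1 − 0.95² = 9.75%, but these tests are strongly correlated. In a further form, baseline, week 6 and week 12 are all responses with unstructured covariance and complete data. Its week-12-minus-baseline contrast is then essentially the change-score comparison, and the figure stays near 5%.

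**The case against.** The strongest reply is that these are secondary endpoints in a condensed article, and that choosing between two secondary analyses is ordinary work for a statistical analysis plan. That stands as a limit on severity. It does not remove the point, because the text does more than stay silent: it commits to a one-way change-score ANOVA, and a plan that followed it would carry that analysis forward.

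Three further replies have weight.

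- The repeated measures model may itself include baseline, so the preferred analysis is compatible with the text. That is true, but the article does not say so and does not make that model decisive.
- The preceding sentence on general linear models may be meant to cover these outcomes too. This cannot be excluded. Even so, a one-way ANOVA carries no covariates, and the covariates listed there do not include the baseline score.
- The sentence covers three kinds of outcome and two methods, so it may be a summary list and not an instruction to run both on each. A change from baseline does not naturally apply to night-time adherence, since current night-time compression users are ineligible. This is a fair reading, and it is a further reason to state which method belongs to which outcome.

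A reader might go further and infer that the plan throws the baseline away or yields a biased comparison. The documents do not support that: a change score uses the baseline, and it is unbiased under randomization. Nor do they support one fixed inflated error rate, because the form of the repeated measures model is not given.

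**Conclusion.** The point holds as a minor improvement. For two secondary outcomes with a stated significance hypothesis, the article names two analyses and designates neither, and the change-score ANOVA is the less efficient choice given the data already collected.

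The loss depends on r, which the article does not give. It is substantial at r = 0.3 (variance ratio 1.54) and small at 0.7 or above (1.18 or less). The power figures also rest on the assumed 0.6 SD difference and 36 evaluable women per arm. The excess false-positive chance arises only if either result may be used to claim benefit, and it can be close to nil for one form of the model. The primary analyses, the sample size and data collection are not affected.

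**What to change.** Name one deciding analysis for sleep and self-efficacy: a repeated measures model of the week-6 and week-12 scores, with baseline score, centre and lymphedema category as covariates. Read from it the two week-12 contrasts that hypothesis 3 names, NCSG against CB and NCSG against standard care. Keep weeks 18 and 24 out of this model, since the comparison groups have by then moved to the garment. Delete the one-way ANOVA on change scores for these outcomes, or label it descriptive. State the method for adherence-related outcomes separately.

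The cost is a change of wording in the analysis section. No extra measurement, visit or participant is needed.

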### Objectives

The primary objectives of the randomized controlled phase of the trial are to determine the effect of night-time compression on arm lymphedema volume maintenance and quality of life in breast cancer survivors who have completed intensive reduction treatment for their lymphedema. These questions are seen as valuable for informing implementation of night-time compression as a self-management strategy for lymphedema in the clinical setting. The primary objectives of follow-up are to evaluate the long-term adherence to use of night-time compression and the timing of the intervention effect. As well, this follow-up period will allow us to better understand who may benefit the most (or least) from the addition of night-time compression.

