**Fig. 3 Fig3:**
[figure not shown]
Study schema

The randomized fast-track trial (with delayed assignment to NCSG for both comparison groups) is seen as a more acceptable design to patients, families and staff, given that the majority of eligible participants will have a strong preference for assignment to the NCSG group. Moreover, we feel this design, which was used in the pilot study, will optimize recruitment and retention of the comparison group participants in the trial.

The follow-up period after the intervention (weeks 13 to 24) will follow a longitudinal observational design and provides an opportunity to examine factors related long-term adherence to night-time compression.

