#### Group 1: standard care: day-time use of compression sleeve alone

Women randomized to the standard care group will receive standard care for lymphedema maintenance. In this group of the trial, each participant will be instructed to wear their day-time compression sleeve with or without a gauntlet/glove (worn if swelling in the hand and fingers), providing a minimum of 30 mm Hg of pressure, for 12 h per day, each day of the week. A 6-week follow-up will be performed to evaluate response and adherence to the standard care protocol. At week 12, women in this arm of the trial will be fitted for a NCSG and will follow the protocol outlined in the experimental arm of the trial.

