#### Group 3: standard care plus Night-Time Compression System Garment (NCSG group)

Women randomized to the immediate NCSG group will be measured for a NCSG. Once the garment has arrived, participants in this group will be instructed in use of their NCSG by the physical therapist. Educational materials related to garment application and maintenance will be provided. Participants will have a 2-week phase in period, following which they will be asked to wear the NCSG at night while sleeping for a minimum of 8 h per night, a minimum of five nights per week for 4 weeks (weeks 3–6). As per standard of care, each participant will be required to wear their day-time compression sleeve with or without a glove/gauntlet, providing a minimum of 30 mm Hg of pressure, for 12 h per day, each day of the week. A 6-week follow-up will be performed to evaluate response, adherence to the protocol and to address any issues with wear of the NCSG. At that point, maintenance NCSG a minimum of 3 nights per week will be introduced. After the 12-week assessment, participants in this arm of the trial will have the option to continue use of their NCSG.

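### For arm volume and Lymph-ICF, the only analysis named for weeks 13–24 is within-group, which cannot isolate a garment effect or show whether an immediate or a delayed start matters

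*Protocol article*

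**What the plan says.** The Objectives section states: "The primary objectives of follow-up are to evaluate the long-term adherence to use of night-time compression and the timing of the intervention effect". It does not define timing.

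The design is a randomized fast-track trial "with delayed assignment to NCSG for both comparison groups" (Methods/Design, text under Figure 3). For the standard-care and bandaging (CB) arms, Methods/Design adds: "Participants in these two groups will follow the protocol as per the NCSG group during weeks 13 to 24". For standard care, the Group 1 section says: "At week 12, women in this arm of the trial will be fitted for a NCSG". In the arm that starts with the NCSG, the Group 3 section says that after the week-12 assessment "participants in this arm of the trial will have the option to continue use of their NCSG".

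All arms are measured at weeks 6, 12, 18 and 24 (Recruitment). Women who cannot continue their assigned treatment stay in their randomized group (Blinding).

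On analysis, the Statistical analyses section gives a week-12 comparison of the three groups as primary. For the later period it says: "Within group analyses will also be conducted for primary and secondary outcomes from weeks 13 to 24 following completion of all follow-up measures". It also says: "Sleep quality, self-efficacy, and adherence-related outcomes will be analyzed by repeated measures modeling and one-way ANOVA on change scores". That sentence names neither arm volume nor Lymph-ICF and gives no time window. Adherence in weeks 13–24 is to be examined by originally assigned group.

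**The concern.** A before-after change in a single arm has no concurrent comparator. Whatever would have happened to arm volume anyway over weeks 13–24 goes into the estimate in full. The Background reports a cohort in which volume rose gradually after intensive reduction treatment, most in the first year, so some drift is to be expected. A rise would tend to mask a benefit of the garment in the arms that switch to it. Drift common to two randomized arms cancels in the difference between them.

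Within-arm results also cannot say whether women offered the garment at the start end up better at week 24 than women offered it 12 weeks later. If timing includes that question, the named analysis does not address it for the two primary outcomes, although the trial will hold the randomized data that do. The stake is the interpretation of a stated follow-up objective, not the week-12 result.

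**Working it through.** **1. The plan's own figures.** Inputs from the sample size section: 36 per group, volume difference 20, SD 25, alpha 0.05.
- One-way ANOVA with means 0, 10, 20: noncentrality = 36 × (10² + 0² + 10²) / 25² = 11.52, with 2 and 105 degrees of freedom. Power is 85.9% (stated: 86%).
- Lymph-ICF, difference 15, SD 22, Mann-Whitney (sample size multiplied by 3/π): 79.6% (stated: 80%).
- 108 / 0.9 = 120 recruited, as stated.

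The document gives no figure for weeks 13–24.

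**2. What drift does to a within-arm test.** The within-person correlation is not given; 0.5 to 0.7 is assumed. SD of change = 25 × √(2(1 − ρ)), which is 25.0 at ρ = 0.5 and 19.4 at ρ = 0.7. Dividing by √36 gives standard errors of 4.2 and 3.2. The chance that drift alone, with no garment effect, gives a significant two-sided within-arm test is:

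| Drift (points, either direction) | ρ = 0.5 | ρ = 0.7 |
|---|---|---|
| 0 | 5% | 5% |
| 5 | 22% | 33% |
| 10 | 65% | 85% |

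The table shows how sensitive the test is to drift. With rising volume, a significant result would appear as worsening, and a true benefit would be understated by the size of the drift. For example, an assumed benefit of 10 with an assumed rise of 5 shows as an improvement of 10 − 5 = 5.

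**3. Comparing significance across arms does not help.** If two arms have the same true change and each test has power p, the chance that one is significant and the other is not is 2p(1 − p). That is 50% at p = 0.5 and 32% at p = 0.8.

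**4. What the randomized contrast would deliver.** NCSG versus standard care at week 24, assuming SD 25 (volume), SD 22 (Lymph-ICF) and 36 analysed per arm still hold.
- Volume: SE = 25 × √(2/36) = 5.9. The 95% half-width is 1.96 × 5.89 = 11.5, or slightly more (below 12) with the t quantile. The difference detectable with 80% power is (1.96 + 0.84) × 5.89 ≈ 16.5.
- Lymph-ICF: SE = 22 × √(2/36) = 5.2; half-width about 10.2; detectable difference about 14.5.

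| True difference | Volume power | Lymph-ICF power |
|---|---|---|
| 5 | 13% | 16% |
| 10 | 39% | 48% |
| 15 | 71% | 81% |

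The contrast is therefore best reported as an estimate with an interval.

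**The case against.** The strongest reply is that the plan fits its declared design. The article calls weeks 13–24 observational, marks week 12 as the end of the randomized portion, and justifies delayed assignment by acceptability, recruitment and retention. It draws no causal conclusion from within-group change. It is also a condensed article, and a secondary model by arm could sit in an analysis plan that is not shown. This limits the weight of the point. It does not remove the mismatch, because the article itself states an objective and then names an analysis that does not fully serve it. The observational label does not undo the randomization.

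Second, timing is undefined. Methods/Design describes a small early reduction and then a plateau after about 6 weeks. If timing means onset or plateau, within-arm trajectories describe it, though without control, and the randomized week-6 and week-12 data bear on it. The Discussion lists, among practitioners' aims, learning when garments are best prescribed. That favours the early-versus-late reading but is not the trial objective. A reader might infer that the objective definitely asks about delayed start; the text does not settle that.

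Four other stronger readings are not supported:
- **That every outcome is analysed only within groups.** The repeated-measures models for sleep and self-efficacy have no stated window and may run to week 24.
- **That within-arm tests would manufacture a benefit.** The documented drift is upward and would tend to hide one.
- **That regression to the mean is a main source of bias.** Women are selected on volume at entry, not at week 12, so most of it should be spent by then.
- **That the week-24 contrast has 92% power.** That figure is for a 20-point difference, the size planned at week 12 against no night-time compression. Once both arms have been offered the garment, so large a gap is unlikely.

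The randomized contrast has its own limits, and these objections stand. NCSG wear in group 3 is optional after week 12. The delayed arms wait for a garment and have shorter exposure, which does not cancel. The CB arm already had night-time compression, so it is not a clean delayed-start comparator. Blinded assessment is stated only for weeks 6 and 12.

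**Conclusion.** The point holds for arm volume and Lymph-ICF. Their only named analysis in weeks 13–24 cannot separate an NCSG effect from drift and cannot show whether immediate or delayed start matters, while a primary follow-up objective concerns timing. A randomized-arm estimate at weeks 18 and 24 is available from data already planned and is better suited to that objective.

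Its value is an estimate of a difference between policies, not a well-powered test: it is informative mainly for differences of about 15 points or more. This rests on the assumption that the planning SDs and 36 women per arm carry over to week 24. The drift calculation also rests on an assumed correlation of 0.5 to 0.7. The week-12 primary comparison is not touched, so this is a worthwhile low-cost improvement and not a threat to the trial's main conclusion.

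**What to change.** - State what timing means: onset or plateau of the effect, immediate versus delayed start, or both.
- Add a secondary longitudinal model for arm volume and Lymph-ICF by randomized arm, with arm-by-visit terms over weeks 6, 12, 18 and 24, adjusted for baseline, centre and lymphedema severity.
- Report the NCSG minus standard-care difference with 95% confidence interval at weeks 18 and 24, labelled as immediate versus delayed offer of NCSG.
- Keep within-arm changes as descriptive, and do not compare arms by which of them reach significance.
- Make no claim of high power for these contrasts, and state their limits: optional wear in group 3, garment wait and shorter exposure in the delayed arms, the prior night-time compression of the CB arm, and no stated blinding after week 12.

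The cost is wording and analysis time. No visits, measurements or participants are added.
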